### Blinding

It is not possible to blind either patients or treating surgeons as to when the patient has had surgery or whether they have had surgery. To minimize possible sources of bias, randomization is undertaken centrally, thus ensuring concealment of allocation from the enrolling clinician, patient, and relatives. All patients randomized, for whom outcome data can be collected, will be included in the analysis by intention to treat. The multidisciplinary team in the co-ordinating center and the principal investigators will be blinded to the results until after the data set is locked following receipt of the final outcome questionnaire. Only the data manager will have access to ‘unblinded’ data.

### Statistical analysis

Analysis will be on an ‘intention-to-treat’ basis. The primary analysis will be a simple categorical frequency comparison using the uncorrected chi-squared test for prognosis-based
[13,14] favorable and unfavorable outcomes at 6 months. Patients with a good prognosis will be categorized as having a favorable outcome if they achieve good recovery or moderate disability on the Glasgow Outcome Scale. Patients with a poor prognosis will be categorized as having a favorable outcome if they achieve good recovery, moderate disability, or upper severe disability on the extended Glasgow Outcome Scale. Logistic regression analysis will be undertaken to adjust for covariates. Secondary outcomes will also be analyzed using the prognosis based method as specified in STICH
[3].

Given the likelihood of a proportion of crossovers, a secondary sensitivity analysis of per-treatment as well as an analysis considering crossovers to surgery as failed medical treatment will be undertaken. Further analyses of factors that drive crossovers as well as per-protocol and per-treatment analyses will be conducted to investigate the effect of crossovers.

Any subgroup analyses will be based on tests of interaction. The predefined subgroups (all of which will be considered exploratory, since the study is not powered for formal subgroup analyses) include the following: age; hematoma volume; Glasgow Coma Score; time from injury to randomization; severity of neurological deficit; pupils equal and reacting or not; planned method of hematoma removal; patients with invasive monitoring (ICP/CPP); anticoagulation status.

Interim analyses are conducted at intervals predetermined by the DMEC. The results of interim analyses are strictly confidential and the trial will only be stopped early if one or other treatment policy shows an advantage at a very high significance level, or if recruitment rates are unexpectedly low.

Deterministic and probabilistic sensitivity analyses will be conducted to consider the importance of individual parameters and assumptions in determining cost-effectiveness. This will include the effect of time horizon, variation in unit costs across centers, and quality of life values. Bootstrapped-generated differences in costs and effectiveness between strategies will be computed, and results presented using cost-effectiveness acceptability curves (CEACs).

Receiver-operating curves will be used to investigate appropriate thresholds of ICP and CPP for treatment as they have been used previously in pediatric studies
[15].

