### Randomization (treatment allocation)

Before randomization, a one-page form is completed by the responsible neurosurgeon recording demographic (age, gender) and TICH characteristics (site, side, ABC measures to define volume) and status at randomization (pupils equal and reacting or not). The clinician either telephones the independent 24-h telephone randomization service or accesses the randomization website and enters the randomization information. At the end of the randomization phone call/web data entry process the neurosurgeon is informed of the patient identifier number for the trial and the treatment group the patient is allocated to. The neurosurgeon records this information on the randomization form and then faxes the form to the STITCH(TRAUMA) Office. If the site has problems contacting the randomization service they are able to contact a member of the project team using the study backup number.

The data manager checks this information against the information received from the randomization center and enters the data into an anonymized password protected database. A list of patient names and study numbers are kept in a separate file to ensure patient confidentiality is maintained.

Allocation is stratified by geographic region, with a minimization algorithm based on age group and severity (as measured by whether the pupils are equal and reacting or not) and with a random component (that is, with probability of 80%).

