### Sample size

Previous studies have suggested a favorable outcome in the non-operated group of about 40% and a favorable outcome in the surgical group of about 60% to 70%. However this was in observational studies. Assuming a favorable outcome (good recovery or moderate disability on the Glasgow Outcome Scale) of 50% from conservative treatment a total sample size of 776 would be required to show a 10% benefit (that is, 50% *vs.* 60%) from surgery (2p <0.05) with 80% power. A safety margin of 9.5% is built in to allow for loss to follow-up making a total sample size of 840 to be recruited and randomized (420 per arm).

In order to achieve this sample size in a reasonable time span and to provide robust evidence it is necessary to recruit patients from outside UK. In England and Wales there are only 30 neurosurgical units and only one-third of these participate in randomized controlled trials. Experience with interested neurosurgical centers in previous studies has shown that about 25% of recruited centers fail to recruit any patients and a further 25% only recruit one or two patients. The best recruiting centers will recruit about 10 patients per year so to complete patient recruitment within the timescale we will approach at least 150 centers.

Loss to follow-up is kept as low as possible. In the STICH study the loss was about 5%. In STITCH(TRAUMA) the population is a little younger and likely to be more mobile; however, we carry out more checks and implement procedures that we have developed to minimize loss to follow-up. Methods of follow-up are adapted to those most likely to be successful within each country and center according to local population and care characteristics. Centers that achieve poor follow-up are monitored closely and may be withdrawn from the study if they are unable to locate patients for 6-month follow-up. We require residence in any study country as an eligibility criterion so patients who suffer a head injury whilst on holiday and might be lost to follow-up are not eligible and are not included.

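### The unadjusted chi-squared primary test ignores the factors balanced at allocation; it is valid and keeps its 80% power, but gives up some efficiency if those factors predict outcome

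*Protocol article*

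**What the plan says.** Three sections of the protocol article bear on this.

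- **Randomization (treatment allocation):** "Allocation is stratified by geographic region, with a minimization algorithm based on age group and severity". Severity means whether the pupils are equal and reacting, and the algorithm has a random element given as 80%. The Trial design section says the same in brief.
- **Statistical analysis:** "The primary analysis will be a simple categorical frequency comparison using the uncorrected chi-squared test", applied to favorable versus unfavorable outcome at 6 months. The cut for a favorable outcome is lower for patients with a poor prognosis. The section then adds: "Logistic regression analysis will be undertaken to adjust for covariates". It does not make this model primary.
- **Sample size:** "Assuming a favorable outcome (good recovery or moderate disability on the Glasgow Outcome Scale) of 50% from conservative treatment", a total of 776 "would be required to show a 10% benefit" (50% versus 60%) "from surgery (2p <0.05) with 80% power". Recruitment is set at 840.

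**The concern.** Balancing the arms on region, age group and pupils makes the difference in proportions less variable between hypothetical repeats of the trial, provided those factors predict outcome. The chi-squared variance does not know this: it still contains the between-stratum variation that allocation has largely removed. The standard error is then somewhat too large, the confidence interval somewhat too wide, and the test rejects a true null less often than 5%. A model that includes the factors recovers that precision.

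The design itself treats these factors as important. It uses pupils as its measure of severity, and it names both age and pupils as subgroups. At stake is power that needs no extra patients, in a trial that plans to approach at least 150 centers to reach its target.

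**Working it through.** **1. Reproduce the planned sample size.** Inputs from the Sample size section: 50% versus 60%, two-sided 0.05, 80% power. With pooled variance under the null and no continuity correction:

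n per arm = [1.960 × √(2 × 0.55 × 0.45) + 0.8416 × √(0.50 × 0.50 + 0.60 × 0.40)]² / 0.10² = (1.379 + 0.589)² / 0.01 = 387.3, so 388 per arm and 776 in total.

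This matches the article exactly (power 80.1%). With continuity correction the total would be 816, and with unpooled variance 770. The sample size is therefore the right one for the uncorrected chi-squared test.

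**2. Approximation with perfect balance.** Let R² be the share of outcome variance explained by the allocation factors. If they are perfectly balanced, the chi-squared z statistic has null variance 1 − R². Then:

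- type I error of chi-squared = 2 × [1 − Φ(1.960 / √(1 − R²))]
- power of chi-squared ≈ Φ(0.8416 / √(1 − R²))
- power of the adjusted test ≈ Φ((1.960 + 0.8416) / √(1 − R²) − 1.960)

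Worked for R² = 0.10: √0.90 = 0.9487. Type I error = 2 × [1 − Φ(2.066)] = 0.039. Chi-squared power = Φ(0.887) = 0.81. Adjusted power = Φ(2.953 − 1.960) = Φ(0.993) = 0.84.

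| Assumed R² | Type I error, chi-squared | Power, chi-squared | Power, adjusted |
|---|---|---|---|
| 0 | 0.050 | 0.80 | 0.80 |
| 0.05 | 0.044 | 0.81 | 0.82 |
| 0.10 | 0.039 | 0.81 | 0.84 |
| 0.20 | 0.028 | 0.83 | 0.88 |

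**3. Simulation with imperfect balance.** N = 776, minimization within region on age group and pupils, with probability 0.8 of assigning the arm that reduces imbalance, and 4,000 trials per scenario. Marginal rates were 50% versus 60%, or equal under the null. The article does not give the layout, so this was assumed: five equal regions, three age groups (35%, 40%, 25%) and abnormal pupils in 20%. The adjusted analysis is a logistic regression on treatment, region, age group and pupils.

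| Assumed R² (AUC) | Type I error: chi-squared / adjusted | Power: chi-squared / adjusted |
|---|---|---|
| 0 (0.50) | 0.045 / 0.047 | 0.79 / 0.79 |
| 0.03 (0.60) | 0.047 / 0.056 | 0.82 / 0.83 |
| 0.10 (0.67) | 0.039 / 0.049 | 0.81 / 0.84 |
| 0.18 (0.74) | 0.032 / 0.052 | 0.82 / 0.87 |

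Monte Carlo standard error is about 0.0035 for type I error and 0.006 for power. The first two rows are compatible with 0.05 for both tests. At R² of 0.10 and 0.18 the conservatism is clear and agrees with step 2.

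**4. Effect of the prognosis-based cut.** A lower bar for poor-prognosis patients weakens the link between baseline factors and outcome. As an illustration, take a standard normal predictor with a log-odds slope of 1.0, which on a fixed cut gives R² = 0.174 and AUC 0.74. Shift the log-odds of a favorable outcome upward for the worse-prognosis half, then apply the formulas in step 2.

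| Assumed shift (logits) | R² | Type I error, chi-squared | Gain from adjustment |
|---|---|---|---|
| 0 | 0.174 | 0.031 | 86.9% − 82.3% = 4.6 points |
| 0.5 | 0.120 | 0.037 | 84.8% − 81.5% = 3.3 points |
| 0.8 | 0.097 | 0.039 | 83.9% − 81.2% = 2.7 points |
| 1.1 | 0.082 | 0.041 | 83.3% − 81.0% = 2.3 points |

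The half split and the shifts are assumptions. The direction follows from the endpoint definition.

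**The case against.** The strongest reply is that nothing here is an error. The chi-squared test has type I error at or below 5%, the sample size was computed for exactly this test, and an adjusted analysis is already planned. The dispute is only about which of two planned analyses is primary. The choice of covariates for the logistic regression may properly be left to an analysis plan that is not shown. All of this stands.

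The reply also notes that the loss is conditional: if region, age group and pupils do not predict this outcome, there is nothing to gain. That stands too, and step 3 shows it.

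A reader might infer two stronger things. One is that the trial is underpowered because of this choice. It is not: step 1 gives 80% for the test named. The other is that the primary test rejects only 2% to 3% of the time under the null and that adjustment would lift power to about 90%. That requires tight balance on a strong continuous predictor of the outcome. The trial balances region, age group and a binary pupil item, with a random element, and its endpoint already absorbs part of baseline prognosis. The article gives no prognostic strength that would support such figures.

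The reply does not answer why factors important enough to govern allocation should be left out of the headline test. A further analysis does not change the standard error or the p-value of the primary one.

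**Conclusion.** The point holds as a matter of efficiency, not validity. The primary test omits the factors that the allocation balances, and to the extent that they predict outcome it is mildly conservative and less powerful than an adjusted test. The plausible loss is roughly 1 to 5 power points, with type I error between about 0.047 and 0.032 over assumed R² of 0.03 to 0.18. The lower part of that range is more likely, given the prognosis-based cut. If the factors are not prognostic there is no loss.

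The direction is certain once the factors are prognostic. The size rests on assumed prognostic strength and an assumed stratum layout, because the article gives neither. The planned 80% power at 776 is unaffected.

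**What to change.** Before unblinding, amend the Statistical analysis section as follows.

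- **Primary analysis:** logistic regression of the same 6-month prognosis-based outcome on treatment, region, age and pupil reactivity.
- **Small regions:** pool them by a prespecified rule, since the number and size of regions are not given and some may be sparse.
- **Primary estimate:** the standardized (marginal) risk difference with 95% CI, because the trial is powered on a 10-point difference in proportions. Report the adjusted odds ratio alongside.
- **Supportive analysis:** the uncorrected chi-squared test, unchanged.
- **Optional:** hematoma volume as a further prespecified covariate. It is not an allocation factor, so the argument above does not depend on it.

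The cost is a short change of text and a less simple primary test. Age, pupil status and hematoma measurements are on the randomization form, and region is the stratifier, so no new data are needed. The sample size is unchanged. In the simulation the adjusted test stayed close to 5% and lost no power when the factors were not prognostic.

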[2]. Patients suffering a TICH tend to be younger by about 15 years on average than patients suffering a spontaneous ICH and therefore the level of disability may have a large effect on their ability to return to work and their economic output. Traumatic ICHs are more likely to be lobar, to be superficial, and to have a medium-sized volume (25 to 65 cc). These differences between the conditions mean that we cannot derive the role of surgery for TICH from results of the 13 published trials of surgery for spontaneous ICH but the STICH trial showed a trend towards better outcome with surgery for the group of spontaneous supratentorial ICH that are most like TICH: superficial hematomas with no intraventricular bleed
[3].

We already know that surgery is effective in patients with traumatic EDH and SDH and that early surgery is better than delayed. This is not known for TICH. If early surgery is of benefit to these patients, then implementation of early referral and diagnosis with immediate treatment may reduce death and disability in this specific group of head-injured patients.

Several authors
[4-6] have compared surgery with conservative treatment in single center retrospective series and recommended surgery for larger TICHs even if patients were in an apparently good clinical state initially. Matheisen *et al.*[4] found that patients with an admission Glasgow Coma Score of at least 6 and a lesion volume of at least 20 mL who had surgery without previous neurological deterioration had significantly better outcomes than those who did not have surgery or had surgery after deterioration. None of the patients who had surgery before any deterioration died or were vegetative as opposed to 39% of those who had surgery after deterioration and 50% of those who did not have surgery. Choksey *et al.*[5] found that 38% of patients with a low GCS and a volume of the TICH >16 mL who had surgery had a poor outcome compared to 56% of those who did not have surgery. Zumkeller *et al.*[6] found that the poor outcome rate in the operated patients was 29% compared to 59% in the non-operated group. Such associations do not represent true causes and effects or treatment benefits or harm.

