### Compliance

Patients or their relatives may withdraw consent for an operation, or conversely request an operation after randomization, thereby leading to crossover between the arms. These are rare events but in surgical trials it is common for the patient’s condition to change over time and a patient randomized to initial conservative treatment may deteriorate and require surgery later. Such crossovers and the reasons for them are documented. Information is collected about the status (GCS and focal signs) of patients through the first 5 days of their trial progress and ICP/CPP measures in invasively monitored patients in order to be able to describe the change in status that leads to a change in equipoise for the treating neurosurgeon, and subsequent surgery in patients initially randomized to conservative treatment.

Compliance with treatment allocation is monitored by the data manager.

In surgical trials patients allocated to the non-surgical arm of the trial may later deteriorate and surgeons may intervene. This was the case in the MRC-funded STICH trial
[3], in trials of cardiac surgery compared with angioplasty, in the MRC-funded back pain trial
[10] and in the SPORT trials
[11]. These crossover rates to surgery were 26%, 28%, 28%, and 30%, respectively. While surgical trials will always have such crossovers when surgeons perceive that there is value in operating on patients who deteriorate after initial randomization into the conservative limb of the trial, we must understand, monitor, and report the rates of such crossovers.

The aim is to achieve as high compliance as possible but experience and the above literature suggest that it is neither practical nor ethical to have 100% compliance with conservative treatment. During the recruitment of centers and at investigator meetings the importance of clinical equipoise and minimizing crossovers is emphasized and any crossover occurring within 12 h of randomization is investigated. Centers exhibiting high crossover rates may be withdrawn from the study.

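### The planned crossover analyses sort, drop or re-score patients by an event after randomization, so none gives an unbiased treatment effect; a randomization-based estimate should be added and the rest labelled descriptive

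*Protocol article*

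**What the plan says.** All places are in the Protocol article.

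- Statistical analysis, primary: "Analysis will be on an ‘intention-to-treat’ basis". The test is fixed: "The primary analysis will be a simple categorical frequency comparison using the uncorrected chi-squared test for prognosis-based" outcomes at 6 months.
- Statistical analysis, crossovers: a per-treatment analysis is planned as a secondary sensitivity analysis, together with one that treats crossover to surgery as failure of medical treatment. The section then adds: "Further analyses of factors that drive crossovers as well as per-protocol and per-treatment analyses will be conducted to investigate the effect of crossovers".
- Compliance: crossovers because patients or relatives change their minds are called rare. The common case is that "a patient randomized to initial conservative treatment may deteriorate and require surgery later", and this is called a crossover. Four earlier surgical trials or trial groups are cited, with crossover rates to surgery of 26%, 28%, 28% and 30%.
- Trial interventions: the conservative policy itself includes evacuation later than 12 h after randomization if it becomes appropriate.
- Background: on retrospective comparisons of operated and non-operated patients, the article says: "Such associations do not represent true causes and effects or treatment benefits or harm".

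**The concern.** If conservative patients are operated on mainly because they deteriorate, surgery received is a marker of prognosis after randomization. A per-treatment analysis moves deteriorated patients into the operated group. A per-protocol analysis that removes crossovers deletes them from the conservative arm only. Both leave a non-operated group enriched for patients who did not deteriorate. Scoring crossovers as failures keeps the randomized arms, but it turns some favorable 6-month outcomes into unfavorable ones, in the conservative arm only.

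So the methods named for studying crossovers cannot separate the effect of surgery from selection or re-scoring. The Background declines to read operated versus non-operated comparisons causally, and the Statistical analysis section attaches no such caution to its own. The stake is interpretation. If the intention-to-treat result is null or modest, these analyses will be read for what surgery really does, and they can move by as much as the 10-point design effect in either direction with no true effect present.

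**Working it through.** **Step 1. Reproduce the design figure.** The Sample size section takes a 50% favorable rate in the conservative arm and states that "a total sample size of 776 would be required to show a 10% benefit". The contrast is 50% against 60%, tested two-sided at 5% with power 80%. With pooled variance and no continuity correction:

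n per arm = [1.96·√(2·0.55·0.45) + 0.8416·√(0.5·0.5 + 0.6·0.4)]² / 0.10² = (1.379 + 0.589)² / 0.01 = 387.3, rounded up to 388, or 776 in total. The stated figure is reproduced.

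**Step 2. Model with no true effect.** Inputs:
- 388 per arm and 50% favorable (Sample size), here in both arms.
- Crossover share x = 0.28, within the 26% to 30% cited under Compliance.
- Favorable rate among crossovers f = 20% to 40%. The document does not give this; it is an assumption.
- Full compliance in the surgical arm, also an assumption (relaxed in step 5).

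Formulas:
- Operated patients: (0.5 + x·f)/(1 + x)
- Conservative patients never operated: (0.5 − x·f)/(1 − x)
- Per-treatment difference: first minus second
- Per-protocol difference, if all crossovers are excluded: 0.5 minus the second
- Crossovers scored as failures: conservative rate 0.5 − x·f, so the difference is x·f

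**Step 3. Results at x = 0.28** (differences in points, surgery minus conservative, from unrounded rates; in brackets, the share of trials nominally significant at two-sided 5%).

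| f | Operated | Not operated | Per-treatment | Per-protocol | Crossover = failure |
|---|---|---|---|---|---|
| 20% | 43.4% | 61.7% | -18.2 (over 99%) | -11.7 (85%) | +5.6 (35%) |
| 30% | 45.6% | 57.8% | -12.2 (90%) | -7.8 (51%) | +8.4 (65%) |
| 40% | 47.8% | 53.9% | -6.1 (37%) | -3.9 (17%) | +11.2 (88%) |
| 50% | 50.0% | 50.0% | 0 (5%) | 0 (5%) | +14.0 (98%) |

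For f = 30% the per-treatment line is (0.5 + 0.084)/1.28 = 45.6% against (0.5 − 0.084)/0.72 = 57.8%. The last row is the case where crossover is unrelated to prognosis: the first two biases vanish and the third does not.

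**Step 4. Other crossover rates, f = 30%.** At 26% the three differences are -11.2, -7.0 and +7.8 points. At 30% they are -13.2, -8.6 and +9.0.

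**Step 5. Unoperated patients in the surgical arm** (x = 0.26, f = 30%). With 5% unoperated, per-treatment is -6.7 points if 10% of them do well and -15.1 if 90% do; per-protocol is -4.9 and -9.1. With 10% unoperated, of whom 10% do well, per-treatment shrinks to -2.5.

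**Step 6. A true benefit of 60% versus 50%** (x = 0.26, f = 30%). Per-treatment is (0.6 + 0.078)/1.26 = 53.8% against 57.0%, or -3.2 points. Per-protocol is 60.0% against 57.0%, or +3.0 points.

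**Step 7. An estimate that keeps randomization.** The complier-average effect is the intention-to-treat difference divided by the between-arm difference in the share evacuated within 12 h. With no true effect the numerator is centred on zero, and so is the estimate, whatever drives crossover.

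**The case against.** The strongest reply has five parts.

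1. The primary analysis is intention to treat and the crossover analyses are secondary. This stands. A reader might infer that the trial's main result is at risk; nothing in the document supports that.

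2. A reader might infer that per-treatment and per-protocol are the only crossover analyses, so that only false harm can appear. The Statistical analysis section also plans the failed-treatment analysis, which errs the other way, and an analysis of what drives crossovers. The reply is right on the facts, but opposite biases do not add up to a valid estimate. At x = 0.28 and f = 30% the results run from -12.2 to +8.4, about 20 points around a true zero.

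3. Trial interventions places evacuation after 12 h inside the conservative policy. A per-protocol set built on that definition keeps most rescue surgery, and the per-protocol figures do not follow. This stands, and those figures are conditional on it. The opposite reading is also open, because Compliance calls later surgery a crossover and per-protocol is aimed at crossovers. Set definitions may sit in an analysis plan that is not shown; the tension between the two sections is in the article itself.

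4. The size, and partly the direction, rest on an assumed f. In the one Background series with such a figure, 39% of those operated on after deterioration died or were vegetative, against 50% of those not operated on. That does not show crossovers doing worse than unoperated patients. The series is observational and does not refute the mechanism, but it means the document supplies no value for f. The crossover rates also come from other trials. Hence a range, and could rather than will.

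5. A complier-average effect with a 12 h boundary says nothing about later rescue surgery, which the plan also wants to study. This stands, so it is an addition and not a replacement.

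**Conclusion.** The concern holds in a limited form. Because the protocol expects crossover to follow deterioration, the per-treatment analysis, and the per-protocol analysis if it excludes surgery after 12 h, select on prognosis after randomization. The failed-treatment analysis re-scores one arm only. None is an unbiased treatment effect. With no true effect and the step 2 assumptions, the apparent differences could be about -18 to -6, -12 to -4 and +6 to +11 points respectively, against a design effect of 10. These figures illustrate and do not predict. They depend on an outcome rate among crossovers that the document does not give, on crossover rates borrowed from other trials, and on compliance in the surgical arm. It would go beyond the document to say that the analyses will show harm. The point is worth correcting in the analysis wording and does not call the design into question.

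**What to change.** In Statistical analysis:

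- Add a complier-average causal effect as the crossover sensitivity analysis. Use randomized allocation as the instrument and evacuation within 12 h of randomization as treatment received, which is the boundary under Trial interventions. State the exclusion assumption: allocation affects outcome only through early surgery.
- Keep the per-treatment, per-protocol and failed-treatment results, labelled as descriptive and not as treatment effects.
- Say whether surgery after 12 h in the conservative arm counts as a crossover, and hence who leaves the per-protocol set. Trial interventions and Compliance must be reconciled on this; which reading applies is for the investigators.

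Cost: wording only. Surgery status is already recorded on the two-week/discharge form; confirm that its timing is too. Randomization, sample size and care do not change. The downside is an assumption that the data cannot test and a wider confidence interval. If all 28% of crossovers fell within 12 h and the surgical arm complied fully, the interval would be 1/0.72 = 1.39 times as wide as for intention to treat; fewer early crossovers would widen it less, and unoperated patients in the surgical arm would widen it more.
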